### Aims

The overarching aim of this project is to evaluate the prerequisites, determinants, and feasibility of implementing PAP for children with obesity in paediatric health care. Quantitative studies will investigate implementation and clinical outcomes, while qualitative studies will explore implementation determinants among different stakeholders.

Specific study objectives are as follows:Study 1: To examine how healthcare professionals and managers perceive working with PAP for children with obesity in terms of coherence, cognitive participation, collective action, and reflexive monitoring and how they perceive acceptability, appropriateness, and feasibility of a PAP intervention and, furthermore, to explore barriers and facilitators for working with PAP for children with obesity.Study 2: To explore experiences, barriers, and facilitators for using PAP for children with obesity among healthcare professionals and managers.Study 3: To evaluate the feasibility and acceptability of a PAP intervention for children with obesity on implementation outcomes and clinical outcomes, with physical activity pattern being the primary clinical outcome variable.Study 4: To explore children’s and parents’ experiences of participating in a PAP intervention, with a focus on perceived barriers and facilitators for implementing PAP.

Specific research questions are presented in Table 1.

**Table 1 Tab1:** Research questions

*Study*	*Preliminary title*	*Research questions*
1	Working with PAP for children with obesity in paediatric health care — a cross-sectional survey	How do healthcare professionals and managers perceive working with PAP for children with obesity in terms of coherence, cognitive participation, collective action, and reflexive monitoring?
		How do healthcare professionals and managers perceive PAP for children with obesity in terms of acceptability, appropriateness, and feasibility of the intervention?
		Is there a difference in the above variables between healthcare units, age groups, or professions?
		What are the perceived barriers and facilitators for working with PAP for children with obesity?
2	Experiences among healthcare professionals and managers of using PAP for children with obesity — a focus group study	What are the experiences of healthcare professionals and managers in paediatric clinics of working with PAP for children with obesity?
		What barriers and facilitators do they perceive related to implementing PAP for children with obesity?

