		Which contextual factors do they consider important when working with PAP?
3	Evaluation of PAP for children with obesity on implementation and clinical outcomes — a single-arm intervention study	Do healthcare professionals’ and managers’ perceptions of PAP and working with PAP for children with obesity change after a PAP intervention?
		Do physical activity patterns of children with obesity and one of their parents change after participation in a PAP intervention?
		Is there a correlation between the child’s and their parent’s physical activity pattern?
		Is there a change in BMI, metabolic risk markers, health-related quality of life, sleep, or self-efficacy or motivation for physical activity after participation in a PAP intervention?
		What is the acceptability and feasibility of the intervention among children and parents?
4	Children’s and parents’ experiences of participating in a PAP intervention — an interview study	What are the experiences of children with obesity and their parents of participating in a PAP intervention?
		Which barriers and facilitators of implementing PAP do children and their parents perceive?
		How do children and parents perceive their (their child’s) behaviour change, if any, with particular emphasis on physical activity behaviour?

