### Data collection and outcomes

#### Implementation outcomes

Implementation outcomes will be measured pre-implementation, post-intervention, and at 12-months follow-up. Data will primarily be collected from healthcare professionals and managers through a web-based questionnaire comprising several validated instruments. Primary implementation outcomes are the four core constructs of the NPT: coherence, cognitive participation, collective action, and reflexive monitoring. They will be assessed using the Normalization MeAsure Development (NoMAD), which measures implementation from an NPT perspective and reflects the four constructs [50, 51]. The validated Swedish version S-NoMAD [52] is used in this project and has been adapted to fit children with obesity and address both healthcare professionals and managers. The S-NoMAD comprises 23 items, answered on 11-point or 5-point Likert-type scales.

Secondary implementation outcomes are the acceptability, appropriateness, and feasibility of implementing PAP in paediatric health care. Acceptability is defined as the perception among stakeholders that a given treatment, service, practice, or innovation is agreeable, palatable, or satisfactory; appropriateness is the perceived fit, relevance, or compatibility of the innovation or evidence-based practice for a given practice setting, provider, or consumer and/or perceived fit of the innovation to address a particular issue or problem; and feasibility is the extent to which a new treatment, or an innovation, can be successfully used or carried out within a given agency or setting [53]. These outcomes will be measured with the Acceptability of Intervention Measure (AIM), Intervention Appropriateness Measure (IAM), and Feasibility of Intervention Measure (FIM) [54], all validated instruments with the purpose of assessing the fit and match of a practice or intervention to a given context, targeting different criteria [54]. The three measures comprise 4 items each, answered on 5-point Likert-type scales. Before use, they were translated and cross-culturally adapted into Swedish and adapted to children with obesity, following established procedures including forward and backward translation and validating the translation using cognitive debriefing [55, 56]. The translation aimed to produce a language version with conceptual equivalence with the original and relevance to the new target culture and context.

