Barriers and facilitators will be explored in two open-ended questions, in which the respondents will be given the opportunity to describe their experiences and thoughts regarding determinants for implementing PAP in their clinic, expressed in their own words. They will also be further explored in the focus group study.

Acceptability of the intervention from the child’s perspective will be measured with the Client Satisfaction Questionnaire (CSQ-8) [57], translated to Swedish and adapted to children and parents. Feasibility for the child to participate in PAP will also be examined by collecting process data on fees, equipment, and transport costs of the chosen physical activity, as well as travel time, time spent at the activity, and at assessments and other contacts during the intervention.

Additional implementation process outcomes will be assessed as follows: recruitment and attrition rates will be examined. When possible and if participants consent, reasons for dropout will be documented. Intervention fidelity (intervention delivery as intended) and dose (quantity of intervention) will be captured by monitoring intervention components delivered. Other simultaneous treatment, e.g. dietary recommendations, will be documented. Availability of local physical activities will be documented. Data regarding intervention adherence and participation in the chosen physical activities will be collected via analogue and/or digital activity diaries.

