### Data analysis

#### Implementation outcomes

Implementation outcome data will be analysed in two steps. First (in study 1, where the purpose of this survey is to assess healthcare providers’ perceptions of PAP treatment with the aim of identifying implementation barriers and facilitators), baseline (pre-intervention) data will be analysed descriptively using absolute and relative frequencies, as well as means and standard deviations. Differences between age groups, years’ of experience, and different professions will be analysed using chi-square tests We will do a subgroup analysis of respondents from the Gothenburg clinics in which PAP has already been implemented, including access to extra support from the PAP clinics. Second (in study 3), in the subset of the study 1 participants in which the intervention is carried out, we will perform longitudinal analysis of changes after participating in the intervention, using data from pre- and post-intervention, and follow-up at 12 months after baseline. Average change over time will be analysed across the three time points using mixed linear modelling, given the assumption that data are normally distributed. Analyses will be per protocol, and missing data will be handled with maximum likelihood estimation. The free text answers to the open-ended questions related to implementation determinants will be analysed using qualitative content analysis [69].

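### Per protocol is the only analysis set named for the Study 3 implementation outcomes, which risks selecting respondents on delivery in a study that asks whether delivery is feasible

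*Protocol article*

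**What the plan says.** Under Data collection and outcomes, Implementation outcomes, the protocol article ranks the measures: "Primary implementation outcomes are the four core constructs of the NPT: coherence, cognitive participation, collective action, and reflexive monitoring". Acceptability, appropriateness and feasibility are secondary. On who answers, it says: "Data will primarily be collected from healthcare professionals and managers through a web-based questionnaire comprising several validated instruments".

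Under Data analysis, Implementation outcomes, the Study 3 step is described in three parts:

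- The sample: "in the subset of the study 1 participants in which the intervention is carried out, we will perform longitudinal analysis of changes".
- The model: "Average change over time will be analysed across the three time points using mixed linear modelling".
- The analysis set and missing data: "Analyses will be per protocol, and missing data will be handled with maximum likelihood estimation".

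No other analysis set is named for these outcomes. The article does not say what makes a professional, a manager or a clinic protocol-compliant. The per-protocol statement belongs to the implementation outcomes; the text on clinical outcomes names no analysis set.

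Two other places bear on the choice. The Study 3 objective under Aims is "To evaluate the feasibility and acceptability of a PAP intervention for children with obesity on implementation outcomes and clinical outcomes". Among the process outcomes, the article lists delivery itself: "Intervention fidelity (intervention delivery as intended) and dose (quantity of intervention) will be captured by monitoring intervention components delivered".

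**The concern.** A per-protocol set ordinarily keeps those who delivered or followed the intervention as planned. Whether a unit or clinician manages that is known only after the start, and it is part of what this study sets out to measure. Restricting the analysis in this way makes the result conditional on implementation having worked. Two of the primary constructs, cognitive participation and collective action, concern whether staff engage with PAP and put it into practice, so selecting on delivery comes close to selecting on the outcome.

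Study 3 has a single arm. The before-after change in the retained respondents is therefore the whole estimate, and no comparison between arms can offset a selection effect. What is at stake is a favourable picture of staff perceptions drawn mainly from those for whom PAP proved workable. That picture could inform the judgement, described under Recruitment of study participants and sample size, on whether full-scale evaluation is worthwhile.

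**Working it through.** The article gives no figure to reproduce, so the check has two parts: a comparison of the statements, and an illustration of size on assumed values.

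**Comparison of the statements**

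1. *Research question.* Table 1 asks, for Study 3, whether professionals' and managers' "perceptions of PAP and working with PAP for children with obesity change after a PAP intervention". It does not confine this to those who delivered PAP as planned.
2. *Sample already restricted.* The analysis text first limits the sample to Study 1 participants where the intervention is carried out. Per protocol comes after that. Either it removes more people, which in ordinary usage means selection on delivery or adherence, or it removes nobody and has no function.
3. *Selection variable.* Fidelity, dose and adherence are listed as process outcomes in their own right. They arise after baseline and are not eligibility criteria.
4. *What the model needs.* A mixed linear model fitted by maximum likelihood can use respondents with incomplete waves. It does not require a per-protocol restriction, and it cannot bring back people whom the analysis-set definition has removed.

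**Size**

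Let *f* be the share of respondents kept, *d*₁ the mean change among those kept and *d*₀ the mean change among those left out.

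- Change in all respondents = *f* × *d*₁ + (1 − *f*) × *d*₀
- Per-protocol change = *d*₁
- Excess = *d*₁ − [*f* × *d*₁ + (1 − *f*) × *d*₀] = (1 − *f*) × (*d*₁ − *d*₀)

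The article gives none of *f*, *d*₁ or *d*₀. The values below are assumptions, in points on a 5-point item scale.

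| Share kept *f* | Gap −0.5 | Gap 0 | Gap 0.5 | Gap 1.0 |
|---|---|---|---|---|
| 0.9 | −0.05 | 0 | 0.05 | 0.10 |
| 0.7 | −0.15 | 0 | 0.15 | 0.30 |
| 0.5 | −0.25 | 0 | 0.25 | 0.50 |

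For example, (1 − 0.7) × 0.5 = 0.15. With *f* = 1 every entry is 0. The sign follows the gap: positive if those left out changed less, negative if they changed more.

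**The case against.** The strongest reply is that the article contains no fidelity threshold for staff or clinics. The only restriction it spells out is to Study 1 participants where the intervention is carried out, and per protocol may mean no more than that. The article is a condensed text, and its data availability statement refers to a complete study protocol that may define the set. This stands in part. A missing definition is not the finding, and a reader who infers that only staff or clinics with delivery as intended will be kept goes beyond the text. But the naming of per protocol as the sole set is a stated choice, and the benign reading leaves the term redundant and misleading.

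A reader might also infer that the change will certainly be overstated. That needs both that people are excluded and that they changed less; the article shows neither, and the table includes zero and negative results.

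A third tempting inference is that per protocol contradicts maximum likelihood in the same sentence. It does not. A clinician can deliver PAP fully and miss the 12-month questionnaire, so maximum likelihood within a per-protocol set is coherent.

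Finally, non-delivery is not hidden: fidelity, dose, adherence and attrition are reported separately, barriers are collected in open questions, and the article disclaims conclusions about effectiveness. The full-scale decision is also not tied specifically to change in these scores. All this limits the consequence. It does not make a delivery-selected set the right main analysis for the question in Table 1.

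**Conclusion.** The point holds as a risk of selection. Per protocol is the only set declared for the longitudinal analysis of the primary implementation outcomes, in addition to an existing restriction. On its ordinary meaning it conditions the result on something the study treats as an outcome.

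Upward bias is the plausible direction if staff who found PAP unworkable are the ones left out and they changed less. Its size cannot be derived from the article. Over the assumed range (50% to 90% kept, gap of 0.5 to 1.0 points) the excess is 0.05 to 0.50 points on a 5-point item; it is zero if nobody is excluded or there is no gap, and negative if the excluded staff changed more. The conclusion rests on the usual meaning of the term, since the article does not define it.

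**What to change.** Replace the analysis-set sentence with wording such as: *The main analysis includes all Study 1 respondents (professionals and managers) in units taking part in the intervention, regardless of fidelity or dose, in the mixed linear model fitted by maximum likelihood. A per-protocol analysis, with the set defined before the data are analysed, is reported as a labelled sensitivity analysis.*

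If no exclusion beyond the units where the intervention is carried out was intended, delete the term per protocol and keep the rest of the sentence.

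This keeps the population of Study 1 participants and the planned model, and needs no new data. It costs about one sentence. The downside is that the estimated change may be smaller.

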#### Clinical outcomes

Descriptive statistics will be used to summarise characteristics of the participants and will be presented as means with standard deviations or frequencies and percentages. For physical activity outcomes, raw accelerometer data will be processed and filtered in several steps to a measure of activity intensity (mg) [58]. Previously developed and tested calibration equations for body positions, activity type, and for activity intensities will be applied [70, 71]. Accelerometer data will be analysed in 3-s epochs in order to accurately detect normal variation in physical activity [58]. Continuous data on physical activity patterns at baseline, 4, 8, and 12 months, will be analysed using multivariate regression analysis for repeated measures, controlled for multicollinearity between intensity levels. To examine potential influences of demographic and parental factors (gender, age, education level, country of birth) on physical activity patterns, the models will be adjusted for these variables. Change in absolute BMI in kg/m^2^ and in metabolic risk markers in mmol/L will be calculated and analysed using mixed linear modelling. Standardised measures for the separate risk factors waist circumference, insulin resistance, systolic and diastolic blood pressure, high-density lipoprotein, and triglycerides will also be combined in a so-called MetS score and analysed using mixed linear modelling. Patient-reported outcomes will also be analysed using mixed linear modelling and adjusted for the same demographic and parental factors. Changes over time will be presented with 95% confidence intervals. The self-efficacy and motivation variables’ potential mediating role for physical activity will also be explored by including these parameters into the models as covariates. Statistical significance will be set at *p* < 0.05.

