For the assessment of clinical outcomes in study 3, we aim to recruit approximately 60 children with obesity who have been prescribed PAP and one of their parents/guardians from the paediatric clinics in Gothenburg and surrounding communities who agree to participate. Because this is a feasibility study, we have not undertaken a formal sample size calculation but aim to include a sufficient number of participants to provide information about practicalities such as recruitment and attrition rates, intervention fidelity, dose, and adherence, as well as for statistical analyses of clinical outcomes. We have also given consideration to the likelihood of a fairly large attrition rate at each time point. Uncertainties about the recruitment procedure, the capacity to achieve an appropriate sample size, and the intervention itself will be considered in terms of feasibility and whether it is of value to proceed to full-scale evaluation. Children and parents will be screened for eligibility by the staff at the participating paediatric clinics in conjunction with their first visit. All who meet the inclusion criteria will be given oral and written information about the study and asked about interest in participating. Inclusion criteria are as follows: being aged 6–12 years, diagnosed with obesity (BMI > ISO-BMI 30), having an insufficient physical activity level according to national recommendations, and having a parent who is willing to participate. Insufficient physical activity level is defined as not reaching the national guidelines recommendation of 60 min of moderate to vigorous physical activity per day [12]. Exclusion criteria are as follows severe psychiatric comorbidity, severe intellectual or physical disability, or planning to relocate outside the study area within 12 months. To support recruitment and reach the desired sample size, site coordinators will be appointed, trained, and provided with adequate study material.

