#### Clinical outcomes

All clinical outcomes will be measured pre- and post-intervention and at 8 and 12 months’ after baseline. The primary clinical outcome will be physical activity level, measured as minutes per day spent in moderate to vigorous physical activity (MVPA) and assessed using the Axivity accelerometer (Axivity AX3, Axivity Ltd., UK). Accelometry is the most commonly used method in clinical and epidemiological research for objective measurement of physical activity, is easy to use for the study participant and the researcher, and has a high sensitivity for detecting changes in physical activity (30). The accelerometer will be placed above the child’s and parent’s hip in an elastic belt and worn 24 h per day for seven consecutive days. In this position, the accelerometer can be used to assess physical activity at different intensities. The accelerometer recording is accompanied by an activity diary to determine bedtime, non-wear time, and sport activities. A strict protocol for data quality assurance (malfunction, spurious data, wear time, valid days) will be used. A project coordinator will provide the accelerometer to the participants together with oral and written instructions, support the participants if necessary, and collect the accelerometer after use. Measurement procedure, quality assurance, data processing, and analysis will be supported by an experienced team at the Center for Health and Performance [58].

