Secondary clinical outcomes will be physical activity patterns (time spent in different types of activities and at different intensity levels, including sedentary time) measured with accelerometry; anthropometric measures, i.e. BMI; and waist circumference, collected from medical charts. Metabolic risk markers will be assessed via blood pressure measures and blood samples, including fasting plasma glucose, high- and low-density lipoprotein cholesterol, insulin resistance, and triglycerides. In addition, patient-reported health-related quality of life will be measured using KIDSCREEN-10 [59], and the child’s sleep will be measured using the Insomnia Severity Index (ISI) [60, 61]. Parents’ perception about their child’s sleep will be measured using the Pediatric Insomnia Severity Index (PISI) [62, 63]. The child’s self-efficacy for physical activity, and motivation for physical activity, will be measured with validated instruments adapted to children with obesity and parents and appropriately translated to Swedish [64–67]. Adverse events will be monitored and documented.

Demographic data on children will be collected at baseline, including age, gender, comorbidities, and country of birth. Data on participating parents/guardians include age, gender, BMI, comorbidities, country of birth, and education level.

To enable missing data analysis, demographic data will also be collected for those who decline participation, when possible.

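### The planned accelerometer model does not make MVPA the single response and, in its classical form, drops any child with a missing visit

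*Protocol article*

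**What the plan says.** Under Data collection and outcomes (Clinical outcomes), the primary clinical outcome is MVPA in minutes per day, from an accelerometer "worn 24 h per day for seven consecutive days". The secondary outcomes include the activity pattern, described as "time spent in different types of activities and at different intensity levels, including sedentary time".

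Under Data analysis (Clinical outcomes), one sentence covers all of these. It begins "Continuous data on physical activity patterns at baseline, 4, 8, and 12 months" and states that the data "will be analysed using multivariate regression analysis for repeated measures, controlled for multicollinearity between intensity levels". MVPA gets no separate model. The covariates named are in the sentence on "demographic and parental factors (gender, age, education level, country of birth) on physical activity patterns, the models will be adjusted for these variables"; self-efficacy and motivation are added for an exploratory look at mediation.

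The neighbouring outcomes are treated differently. Change in BMI and "in metabolic risk markers in mmol/L will be calculated and analysed using mixed linear modelling", and the combined metabolic score and the patient-reported outcomes also get mixed linear models. Maximum likelihood for missing data is stated only under Implementation outcomes.

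On expected losses, the section on recruitment and sample size says: "We have also given consideration to the likelihood of a fairly large attrition rate at each time point". It gives no rate. The target is about 60 children, without a formal sample size calculation.

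**The concern.** Two features of the model sentence fit the primary outcome badly.

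First, it treats the intensity levels as one block and speaks of controlling multicollinearity between them. That phrase usually concerns predictors, whereas here the levels are outcomes. An analyst could put sedentary and light time on the right-hand side of a model for MVPA. The time coefficient would then be the change in MVPA at fixed amounts of other behaviours, not the change in MVPA. The day has a fixed length, so extra MVPA must come from somewhere, and holding the other parts fixed removes some of the change being measured.

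Second, multivariate repeated-measures analysis in its classical form needs a complete set of visits for each child. With four measurement waves and substantial expected attrition, it discards valid recordings from every child who misses one wave.

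At stake are the size and precision of the main clinical estimate that the study would pass to a larger trial.

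**Working it through.** The protocol gives no power or precision figure for MVPA, so there is none to reproduce. The inputs from the documents are 60 children, four visits (baseline, 4, 8 and 12 months) and 24-hour wear. Loss rates and variances are assumptions.

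**Children left under complete-case analysis.** With loss *a* at each of three follow-ups, and no return after dropout, completers = 60 × (1 − a)³.

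| Assumed loss per follow-up | Completers | Pairs at 4 months, 60(1 − a) | Child-visits available | Child-visits used by completers |
|---|---|---|---|---|
| 10% | 43.7 | 54 | 206 | 175 |
| 15% | 36.8 | 51 | 191 | 147 |
| 20% | 30.7 | 48 | 177 | 123 |

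**Precision of the 4-month change.** The standard error varies as 1/√n, so the ratio of completers to available pairs is √[(1 − a)/(1 − a)³] = 1/(1 − a) = 1.11, 1.18 and 1.25.

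At 8 months the same reasoning gives √[1/(1 − a)] = 1.05, 1.08 and 1.12. At 12 months the available pairs are the completers, so this penalty disappears. The loss is therefore greatest at the end of the intervention.

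If a further 10% of recordings per wave were invalid (assumed), completers would be multiplied by 0.9⁴ = 0.656, leaving about 29, 24 and 20.

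**Effect of conditioning on other bands.** The simulation used 60 children, four visits and a true MVPA rise of 10 min/day at every follow-up. Assumed within-child SDs were 10 min for MVPA, 25 for light activity and 20 for sleep, with sedentary time as the remainder of 1440 min. The time effect was estimated within child.

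- No other band: 9.9 to 10.2.
- Given sedentary time: 9.3 to 9.9, depending on whether the rise displaces sedentary or light time.
- Given sedentary and light time: 7.8 to 8.1.
- Given sedentary, light and sleep: exactly 0, because MVPA is then 1440 minus the rest.

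The third result can be checked by hand. Once sedentary and light time are fixed, MVPA plus sleep is known. The slope of MVPA on that sum is 100/(100 + 400) = 0.2, so the rise becomes 10 × (1 − 0.2) = 8.0. The attenuation thus depends on the assumed ratio of MVPA variance to sleep variance. A separate simulation with other assumed compositions gave 8.5 given light and sedentary time, against 9.9 unadjusted. Relative to the true 10, the two runs give about 15–20% attenuation.

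**The case against.** The strongest reply is that the sentence has a sound reading. Multivariate most naturally means several responses modelled together, and such a model does not condition MVPA on anything. Near-redundancy among responses is a real concern there: bands that fill a fixed day have a singular joint covariance, so there is something to control. The covariates actually named are demographic and parental, with self-efficacy and motivation in the exploratory mediation analysis; no intensity band is listed. Multivariate repeated-measures models can also be fitted by likelihood with incomplete visits, and the full protocol, which is not shown, may specify this. All of this stands.

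It rules out several stronger inferences that a reader might draw:

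- **That the plan conditions MVPA on the rest of the day.** This is one reading, not the text.
- **That the analysis would return a zero change.** That is an identity from entering every other component. It is the perfect collinearity that the sentence appears meant to avoid.
- **That no mean change with an interval would be produced.** The same section promises changes over time with 95% confidence intervals, and a joint-response model can supply them.
- **That incomplete children will be dropped, or that completers will be the more active families.** The documents state neither.

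The reply does not remove the ambiguity for the primary outcome. Nor does it explain why this outcome family alone departs from the mixed models used beside it.

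**Conclusion.** The point holds as a badly fixed method for the primary clinical outcome, not as a demonstrated error in the estimate. The governing sentence does not identify MVPA as the single response. It also names a method whose classical form is vulnerable to the attrition that the protocol itself expects.

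The precision figures assume a constant loss of 10 to 20% per follow-up without return, and listwise deletion. The attenuation figures apply only if sedentary and light time enter as covariates, and they depend on assumed variances; with sedentary time alone the effect is small.

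Severity is moderate. This is a single-arm feasibility study that, under Strengths and limitations, already disclaims conclusions on effectiveness and concedes that it may be underpowered. That concession is also a reason not to discard usable visits.

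**What to change.** State a separate model for the primary outcome:

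- MVPA in minutes per day as the only response, in a mixed linear model fitted by REML.
- Visit as a categorical fixed effect, with a random effect for child.
- All available visits from baseline to 12 months included, whether or not the child has all four.
- The planned demographic and parental covariates, and no other intensity band as covariate.
- Mean change from baseline reported with its 95% confidence interval.

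Keep the multivariate analysis of intensity levels as a separate secondary analysis of activity pattern, and say there that the levels are responses. A compositional approach is one option, not a requirement.

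The cost is analysis wording only. No extra data are needed, and the same type of model is already planned for the other clinical outcomes.
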